This study will aim to evaluate the effectiveness of the validated treatment model (IHSS) for the treatment of Indigenous patients with a history of IGT and SUD in a four-week residential treatment centre. Study findings will be used to inform trauma and SUD residential treatment programming and implementation for Indigenous communities across Canada. Hopefully this work will contribute to the field of community-based trauma and addiction programming by addressing objectives that consider:*The patient perspective* does patient satisfaction improve when IHSS methodology for treatment of trauma and SUD replaces an abstinence-focused approach?*The program perspective* do program completion rates improve following the implementation of IHSS intervention?*The community perspective* does the revised program serve a broader range of community members requiring treatment for SUD and IGT? Does the impact of residential addiction treatment on reducing broader health care utilization (through reduced substance use related emergency room presentations and hospital admissions in the year following treatment completion) increase following IHSS implementation?

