## Methods

### Aim

The aim of this study will be to determine whether patients who are treated with the IHSS model will have improved treatment satisfaction (increase of 10% over pre-intervention rates), improved treatment completion (increase of 10% over pre-intervention rates), and a greater reduction in health system usage (substance use related presentations to emergency room and hospital admissions) at one-year follow-up compared to those treated within the abstinence-based model (decrease of 10% over pre-intervention rate).

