### Setting of the study

Benbowopka treats approximately 90 patients per year in a residential addiction treatment program in Blind River Northern Ontario. The study periods will include pre-intervention (April 1, 2013–March 31, 2016) and the post-IHSS intervention study window spanning the 27 months post-IHSS implementation (January 1, 2018–March 31, 2021; *n* > 300). Time periods will be chosen to allow analysis by both calendar year and fiscal year. On every 28-day treatment cycle, participants will be recruited and informed by the staff at Benbowopka about the study and, if interested, a consent will be obtained. The data collection will include data from patients initiating treatment at Benbowopka during the study window. Patient follow-up will occur in the year following treatment completion and/or discontinuation. Anonymized patient records will be linked via Ontario Health Insurance Plan (OHIP) number to the administrative health data at the ICES. ICES, formally known as the Institute for Clinical Evaluative Sciences, is an independent research institute that collects and analyzes data on publicly funded health services for research. The data will be queried in the one year following completion or discontinuation of IHSS at Benbowopka to ascertain the impact of substance use on health outcomes including hospitalization, emergency department visits and opioid-related overdose. For patients with multiple admissions, the date of first admission will serve as the index date for health outcomes evaluation.

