### Study population

We will only include data from first-time patients initiating treatment at Benbowopka, meaning that there will be no previous history of treatment at this center. It is common for patients to cycle between treatment and relapse. Studies have shown that multiple treatment attempts are associated with a higher likelihood of positive outcome [32]. Therefore, we will only include first-time patients to eliminate bias associated with cases involving multiple treatment attempts.

Benbowopka’s residential treatment program collects individual-level data based on standardized assessment screening tools routinely used by the Drug and Alcohol Treatment Information System and the National Native Alcohol and Drug Abuse Program. The cohort for this study will be created by using anonymized patient records from the Ontario Health Insurance Plan (OHIP) number. We will link the OHIP number to the administrative health data at ICES in order to be able to evaluate broad health outcomes for patients after they completed the treatment program. ICES routinely links partner data to its core health systems data holdings. We will then query data in the one year following completion or discontinuation of IHSS at Benbowopka to ascertain *Impact of Substance Use on Hospital Costs* as defined by the Canadian Center on Substance Abuse [42]. ICES linkage will enable virtual follow-up of Benbowopka patients for health systems usage. A detailed timeline can be found in the appendix.

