### Propensity score matching

Logistic regression will be used to define propensity scores for treatment groups (pre and post intervention). The treatment group will be matched 1:1 to control using a caliper width of 0.20 greedy matching [54]. Standardized differences (d) will be calculated for each covariate before and after matching. Standardized difference (d) less than 0.10 will indicate balanced covariates [55]. Propensity score matched data will be analyzed to calculate the effect of receiving treatment post-intervention on each helth system usage outcome using McNemar’s test [56]. Proportions will be used to calculate clinical descriptors including relative risk (RR) and number needed to treat or number needed to harm (NNT/NNH), along with 95% confidence intervals (CI) for each descriptor calculated. All statistical analysis will be conducted on the remote server using SAS Version 9.4 [57]. Data will be reviewed by ICES to insure privacy standards are met.

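### The community aim is a greater reduction in health-system use, but use is defined only for the year after treatment, so no difference in reductions is measured

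*Protocol article*

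**What the plan says.** **The aim.** The Aim section of the protocol article looks for "a greater reduction in health system usage (substance use related presentations to emergency room and hospital admissions) at one-year follow-up compared to those treated" under the abstinence-based model, with a target given as "decrease of 10% over pre-intervention rate". The community question at the end of the Background is put in the same terms. It begins "Does the impact of residential addiction treatment on reducing broader health care utilization" and asks whether that impact becomes larger once IHSS is in place.

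**The data window.** Setting of the study says "Patient follow-up will occur in the year following treatment completion and/or discontinuation" and, of the linked administrative data, "The data will be queried in the one year following completion or discontinuation of IHSS at Benbowopka". Study population repeats this: "We will then query data in the one year following completion or discontinuation of IHSS at Benbowopka". The Data analysis section defines the community primary outcome as substance-related use in the year following treatment.

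**The analysis.** Under Propensity score matching, patients are matched 1:1 across the cohorts, and "Propensity score matched data will be analyzed to calculate the effect of receiving treatment post-intervention on each helth system usage outcome" by McNemar's test, with relative risk and number needed to treat or harm.

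No section mentions use of care before admission, either as an outcome period or as a covariate.

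**The concern.** A reduction is a change from an earlier level, and a greater reduction is a difference between two such changes. Both need use before treatment in each cohort. The stated window supplies only use afterwards. McNemar's test does not fill the gap, because each pair consists of two different patients, one from each cohort, and not one patient before and after treatment.

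What remains is a comparison of levels in the follow-up year. It answers the stated question only if prior use was the same in both cohorts. The article gives reason to doubt that. The Background says that people on prescribed medication, including opioid agonist treatment, could not be admitted under the abstinence model, and it makes serving a broader range of community members an objective of the new one. The admission windows are also years apart (2013 to 2016, and from 2018). At stake is one of the three primary outcomes: a difference in who was admitted could be reported as benefit or harm from IHSS.

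**Working it through.** **The plan's own figure.** The only calculation in the article is the sample size of 65 per group, for a standardized effect of 0.5 at the 0.05 level with power above 80%. It reproduces: 2 × (1.96 + 0.84)² / 0.5² gives 63 per group (64 by the t-test), and 65 per group gives 80.8% to 81.3% power. It is generic and does not bear on this point.

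**The two quantities.** Let B be the proportion of a cohort with substance-related use in the year before admission, and r the relative reduction by the year after. Subscript 0 is the historical cohort and 1 is IHSS.

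- Post-year proportion: P = B × (1 − r)
- Post-year relative risk, which the plan estimates: P1/P0 = (B1/B0) × (1 − r1)/(1 − r0)
- Ratio of changes, which the aim asks about on the relative scale: (1 − r1)/(1 − r0)
- Difference-in-differences, the same on the absolute scale: (P1 − B1) − (P0 − B0)

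The relative risk equals the ratio of changes only when B1 = B0. The factor B1/B0 cannot be recovered from post-year data.

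**Illustration.** All rates below are assumed, because the article gives none. They stand for prior use that remains different after matching.

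| Case | B0, B1 | r0, r1 | P0, P1 | Post-year RR | Ratio of changes | Difference-in-differences |
|---|---|---|---|---|---|---|
| A | 50%, 50% | 20%, 30% | 40%, 35% | 0.875 | 0.875 | −5 points |
| B | 40%, 60% | 20%, 30% | 32%, 42% | 1.31 | 0.875 | −10 points |
| C | 50%, 40% | 20%, 10% | 40%, 36% | 0.90 | 1.125 | +6 points |
| D | 40%, 50% | 25%, 25% | 30%, 37.5% | 1.25 | 1.00 | −2.5 points |

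- A: with equal prior use the two measures agree.
- B: IHSS reduces use more on both scales, yet the post-year comparison shows apparent harm.
- C: IHSS reduces use less on both scales, yet a 10% relative decrease appears to be met.
- D: relative reductions are equal, but the post-year relative risk is 1.25. On the absolute scale the drops are 10 and 12.5 points, which slightly favors IHSS, so the reductions are equal only as ratios.

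**The case against.** The strongest reply is that the 10% target can be read another way. In this article, pre-intervention usually means the historical cohort and not a patient's own year before admission, and the targets for satisfaction and completion are worded in parallel. On that reading the target is a one-year rate 10% below the historical cohort's, and target, outcome and test agree. This stands in part. A reader might infer that the plan can estimate no reduction of any kind. That goes too far, because a between-cohort difference in one-year use is estimable. The reading still does not fit the greater reduction named in the Aim or the Background question about treatment's impact on use, and it leaves prior use uncontrolled.

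Three other inferences are not supported:

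- **That prior use is shut out of the propensity model.** The only covariate list (sex/gender, age, substance type) is in the abstract and is introduced as examples. The matching section names no covariates. What can be said is that the stated query would not retrieve prior use from the linked data.
- **That McNemar's test contradicts an aim about a rate.** The same sentence uses rates for satisfaction and for completion, and completion is recorded as yes or no. Rate may mean a proportion of patients.
- **That the size of the bias is known.** The baselines above are assumed, and the scale of the 10% target is not stated.

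A full protocol, or the timeline appendix that Study population mentions, might contain a look-back period, and the list of administrative databases carries no time limit. But the article itself states the window, the outcome and the test, and these do not fit its aim. The point is therefore a conflict within the text and not a missing detail.

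**Conclusion.** The point holds in this form. The community aim is a difference in reductions. The data window and the matched comparison deliver a difference in one-year levels. The two coincide, on the relative scale, only if prior use is equal in the matched cohorts, and the change in eligibility makes that unsafe to presume.

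The size cannot be fixed from the article. In the assumed cases B and C the conclusion about which model reduced use more is reversed in one direction and then the other. A prior-use ratio of 1.25 between cohorts (case D) moves the relative risk by 25%, which is larger than the 10% target if that target is relative. Matching on age, sex/gender and substance type may narrow the gap in prior use, but nothing in the article shows by how much.

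**What to change.** Extend the ICES request for emergency visits (NACRS) and hospital admissions (DAD) to the 365 days before index admission, for both cohorts. Then choose one of two routes and align the Aim, the Background question, the data window and the analysis section with it.

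- **Route (a): keep the aim.** Estimate the cohort-by-period contrast as a difference-in-differences or a ratio of changes, state the scale, and use standard errors that allow for repeated measures. Do not also match on prior-year use. That would be partly redundant, since balancing the baseline largely returns the contrast to the post-year comparison, and it invites regression to the mean where underlying use differs.
- **Route (b): reword the aim** as lower one-year use than in the historical cohort. Keep the matched comparison and McNemar's test, and include prior-year use in the propensity model.

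Analyzing counts of visits and admissions instead of any event is optional under either route.

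**Cost.** No new patients, procedures or data sources are needed. The data request becomes somewhat larger and must pass through the existing governance process (OCAP principles, consultation with the Chiefs of Ontario) and fit the consent obtained. Patients newly insured in Ontario will have a shorter look-back. Neither route removes era-specific trends in use of care, which should be stated as a remaining limitation.

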### Study population

We will only include data from first-time patients initiating treatment at Benbowopka, meaning that there will be no previous history of treatment at this center. It is common for patients to cycle between treatment and relapse. Studies have shown that multiple treatment attempts are associated with a higher likelihood of positive outcome [32]. Therefore, we will only include first-time patients to eliminate bias associated with cases involving multiple treatment attempts.

Benbowopka’s residential treatment program collects individual-level data based on standardized assessment screening tools routinely used by the Drug and Alcohol Treatment Information System and the National Native Alcohol and Drug Abuse Program. The cohort for this study will be created by using anonymized patient records from the Ontario Health Insurance Plan (OHIP) number. We will link the OHIP number to the administrative health data at ICES in order to be able to evaluate broad health outcomes for patients after they completed the treatment program. ICES routinely links partner data to its core health systems data holdings. We will then query data in the one year following completion or discontinuation of IHSS at Benbowopka to ascertain *Impact of Substance Use on Hospital Costs* as defined by the Canadian Center on Substance Abuse [42]. ICES linkage will enable virtual follow-up of Benbowopka patients for health systems usage. A detailed timeline can be found in the appendix.

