**Methods:**

We will conduct a pre/post Quasi Experimental Community trial, to compare historical treatment outcomes for patients following the implementation of Indigenous Healing and Seeking Safety. We will conduct quantitative and qualitative analyses to understand the differences before and after the intervention is implemented. The pre- Indigenous Healing and Seeking Safety intervention study window will span from 2013 to 2016; *n* = 343, and the post-Indigenous Healing and Seeking Safety intervention study window from 2018 to 2020; *n* > 300. All participants will be enrolled in the Benbowopka residential treatment for the first time during the study periods. All data will be anonymized at the time of data entry. Propensity matching will be undertaken for patient characteristics, including sex/gender, age, and substance use type.

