Outpatient and residential treatment of SUD within Indigenous communities presents many challenges and barriers [2, 24]. Many communities continue to report the need for increased access to evidence-based treatment options [25, 26]. While it appears as though some success has been achieved by treatment models [24, 27, 28]; there is a lack of access and a need for evidence-based treatments [24, 27, 28]. Many communities report a lack of services, specifically Indigenous treatment options and culturally sensitive approaches, as well as a lack of cultural awareness from health care professionals and rehabilitation services [25]. Moreover, there is currently limited knowledge in regard to how well the existing services and treatment centers in northern Ontario are addressing the needs of young people with SUD.

In Canada, there are 49 federally funded adult and youth NNADAP and nine YSAP treatment centres. The majority of NNADAP centres were founded on Western approaches to treatment in the 1980s, and later incorporated Indigenous understandings of healing and personal growth. Therefore, to date the majority of addiction treatment for Indigenous populations in Canada is residential treatment [14]. An addictions service needs assessment study conducted in Ontario First Nations communities—the majority of which were located in northern Ontario—reported that the addiction-related education, promotion and prevention programs in their communities mainly targeted adults [29, 30]. These communities also report the effects of both IGT and SUD and the need for culturally based and culturally safe services, particularly those that are informed by institutional IGT experienced by Canada’s First Nations, Métis and Inuit peoples [29, 31].

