The abstinence model of service that was being delivered at Benbowopka Treatment Centre was excluding many individuals who were seeking residential addictions treatment for problems related to prescription opioids and other drugs. Individuals who were on prescribed medication, including opioid agonist treatment, by their physician to address SUD or mental health challenges were not eligible for admission to Benbowopka Treatment Centre because of its abstinence-based model of service. In 2014, Mamaweswen North Shore Tribal Council directed Benbowopka Treatment Centre to move forward with a plan for the realignment of its services to a harm reduction model of service that would follow the best practice strategies recommended for addictions treatment. Thus, the implementation of the Indigenous Healing and Seeking Safety (IHSS) approach at Benbowopka for Indigenous patients with a history of IGT and SUD was initiated in 2016.

The Mamaweswen (North Shore Tribal Council) and the Benbowopka Treatment Centre represent seven member communities (Batchewana, Garden River, Thessalon, Sagamok, Mississauga, Atikameksheng, and Serpent River) on the North Shore of Lake Huron. Benbowopka treats approximately 90 patients per year in a residential treatment program. The program has high-quality retrospective data based on standardized assessment screening tools routinely used by the Drug and Alcohol Treatment Information System and the National Native Alcohol and Drug Abuse Program.

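### The first-time rule excludes only earlier treatment at this centre, so it cannot eliminate bias from multiple treatment attempts; earlier treatment elsewhere may differ between eras, in a direction the article does not fix

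*Protocol article*

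**What the plan says.** The Study population section notes that patients often move between treatment and relapse, and gives the premise: "Studies have shown that multiple treatment attempts are associated with a higher likelihood of positive outcome". From this it concludes: "Therefore, we will only include first-time patients to eliminate bias associated with cases involving multiple treatment attempts". It defines a first-time patient as one starting at Benbowopka, "meaning that there will be no previous history of treatment at this center".

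The Background supplies the context. On other providers: "there are 49 federally funded adult and youth NNADAP and nine YSAP treatment centres". It also refers to outpatient as well as residential treatment of substance use disorders. On admission under the abstinence model: "Individuals who were on prescribed medication, including opioid agonist treatment, by their physician to address SUD or mental health challenges were not eligible for admission". One of the study questions is: "does the revised program serve a broader range of community members requiring treatment for SUD and IGT".

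On adjustment, the abstract states: "Propensity matching will be undertaken for patient characteristics, including sex/gender, age, and substance use type". The Data collection section lists the programme variables; earlier treatment is not among them. The Setting and Study population sections describe a linked-data query covering the year after completion or discontinuation, with no look-back before admission.

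**The concern.** The article names a specific bias, explains why it matters, and says the inclusion rule removes it. The rule is narrower than the bias. It removes repeat admissions to one centre, while the premise concerns treatment attempts in general.

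This matters in a pre/post comparison only if the share of patients with earlier treatment elsewhere differs between the two periods. There is a documented reason why it might. People on prescribed medication, including opioid agonist treatment, were not eligible in the abstinence era, and services then moved to a harm reduction model. Opioid agonist treatment is itself treatment for a substance use disorder, so someone admitted while receiving it is already in care elsewhere and can still be a first-time patient here.

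At stake are the completion and health-usage comparisons, and what the report may claim. Readers would be told that a recognised source of bias had been eliminated when part of it could remain.

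**Working it through.** **1. Does the rule have the stated property?** Set the three statements of the Study population section side by side.

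- Premise: more treatment attempts go with better outcomes. No place of treatment is specified.
- Rule: no earlier treatment at this centre.
- Conclusion: bias from multiple attempts is eliminated.

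The conclusion follows only if nobody in the cohort was treated elsewhere. The Background shows that other residential centres (49 + 9 = 58 nationally) and outpatient care exist. The count says nothing about how many of these patients used them, but the conclusion does not follow from the rule.

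**2. Does anything else shown remove the bias?** Treatment history is not a named matching characteristic, not a listed programme variable, and not covered by the stated linkage window. Initiation of opioid agonist therapy appears in the Data analysis section as a linked outcome, not as a baseline covariate.

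**3. The plan's own figure.** The Design section gives 65 patients per group for an effect size of 0.5, a probability level of 0.05 and power above 80%. A two-sided comparison of means needs n = 2 x (1.960 + 0.842)^2 / 0.5^2 = 62.8, so 63 per group (64 with the t distribution). Power at 65 is about 81%. The figure reproduces and has no bearing here, because a larger sample does not reduce bias.

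**4. Size of the bias.** With no true IHSS effect,

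bias = (share treated elsewhere, post minus pre) x (outcome advantage of a later attempt).

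The article gives neither input, so both are assumptions. A positive sign favours IHSS. Results in percentage points:

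| Difference in share | Advantage 5 | Advantage 10 | Advantage 15 |
|---|---|---|---|
| -20 points | -1.0 | -2.0 | -3.0 |
| 0 | 0 | 0 | 0 |
| +10 points | +0.5 | +1.0 | +1.5 |
| +20 points | +1.0 | +2.0 | +3.0 |
| +30 points | +1.5 | +3.0 | +4.5 |

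**5. Effect on a test.** Further assumptions: completion of 60% without earlier treatment, a 10-point advantage, 300 patients per era, and an unmatched two-sided two-proportion z-test at 5%.

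- Shares 30% pre, 40% post: 63% v 64%, bias +1, rejection rate 5.7%.
- Shares 30% pre, 50% post: 63% v 65%, bias +2, rejection rate 8.0%.
- Shares 30% pre, 60% post: 63% v 66%, bias +3, rejection rate 12.0%.
- Shares 50% pre, 30% post: 65% v 63%, bias -2, rejection rate 8.0%.

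The Aim section sets a 10% improvement in completion over the pre-intervention rate. Read as relative, on 63%, that is 6.3 points; read as absolute, 10 points. A 3-point bias is about half of the first (3 / 6.3 = 0.48) and under a third of the second.

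**The case against.** The strongest reply is that this is a matter of one verb. The centre-specific definition is stated openly, so a reader can see its limit. The matching list is introduced by a word that leaves it open, and covariate choice is commonly settled in an analysis plan or full protocol that is not shown. The standardized assessments may record treatment history even though the article does not itemise it. All of this stands as a reason not to call the missing covariate an error. It does not make the claim true, because no unseen covariate list changes what the inclusion rule screens for.

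A reader might also infer that the bias favours IHSS: later attempts do better, and the later era admitted people already in treatment. The documents do not support that step. They do not say that those once turned away were treated elsewhere and then arrived as first-time patients. They do not say whether agonist treatment counts as an attempt in the sense of the premise, and they give no size for the premise. If the shares ran the other way, the bias would be against IHSS. Newly eligible patients could also be a more severe group with worse outcomes, which would again work against IHSS.

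**Conclusion.** The statement that the first-time rule eliminates bias from multiple treatment attempts is not supported by the article's own definition and should be corrected. The change in admission eligibility is a documented reason for earlier treatment to differ between eras, so residual confounding is a real possibility.

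Its direction and size are not known. Over assumed differences of -20 to +30 points in the share previously treated, and an assumed advantage of 5 to 15 points, the bias is between -3 and +4.5 percentage points, and zero when the shares are equal. The wider positive end reflects the range chosen for illustration, not evidence about direction. In the middle of these ranges the distortion is modest against the 10% target, but the report could not call it eliminated.

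**What to change.** 1. In the Study population section, replace *to eliminate bias* with *to exclude previous treatment at this centre*, and list treatment elsewhere as a residual source of confounding.
2. From the ICES linkage already planned, derive an indicator of earlier substance-use care over one fixed look-back before first admission, identical in both eras. Add it to the propensity model for the health-usage outcomes.
3. As a sensitivity analysis, repeat both the completion and the health-usage comparisons in patients with no earlier substance-use care on record. This step is needed for completion, because the Propensity score matching section applies the matched analysis to the health-usage outcomes, so a new covariate alone would not reach completion.

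Costs and limits: no new patient contact is required, but the data request grows. Linked records capture residential treatment elsewhere only indirectly, so some patients will still be misclassified, including in the restricted analysis. Patients on agonist treatment at admission may have few or no pre-era matches, so overlap and the number unmatched should be reported. The longer look-back must be covered by the arrangements in the Data governance and ethical considerations section, including the OCAP principles and consultation with the Chiefs of Ontario.
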